**Table 4 Updated Overall Survival Results for 3 Primary Studies in Advanced Melanoma (as of 09-Mar-2009)**

| Parameter                    | CA184022                         | CA184008                          | CA184007                                      |                                                  |
|------------------------------|----------------------------------|-----------------------------------|-----------------------------------------------|--------------------------------------------------|
|                              | All Randomized                   | All Treated                       | All Randomized a                   |                                                  |
|                              | Ipilimumab
10 mg/kg
N = 72 | Ipilimumab 10
mg/kg
N = 155 | Ipilimumab
10 mg/kg +
Placebo
N = 57 | Ipilimumab
10 mg/kg +
Budesonide
N = 58 |
| OS, Median (Months)          | 11.43                            | 10.22                             | 19.29                                         | 17.68                                            |
| 95% CI (Months) b | (6.90, 16.10)                    | (7.59, 16.30)                     | (11.99, --)                                   | (6.80, --)                                       |
| Survival Rate at 1 Year (%)  | 48.64                            | 47.22                             | 62.41                                         | 55.87                                            |
| 95% CI (%) c      | (36.84, 60.36)                   | (39.52, 55.11)                    | (49.37, 75.07)                                | (42.71, 68.79)                                   |
| Survival Rate at 2 Years (%) | 29.81                            | 32.83                             | 41.78                                         | 40.57                                            |
| 95% CI (%) c      | (19.13, 41.14)                   | (25.37, 40.49)                    | (28.30, 55.46)                                | (27.12, 54.37)                                   |

a Data are presented for the per-protocol mixed population of pretreated and previously untreated subjects.

b Based on Kaplan-Meier estimation and CI computed using the bootstrap method.

c Median and associated 2-sided 95% CIs calculated using the method of Brookmeyer and Crowley.

Consistent with the known mechanism of action of ipilimumab, the reduction in tumor burden in the 3 primary melanoma studies was characterized by novel patterns of measurable clinical effect. In addition to objective response (complete response [CR] and partial response [PR]), and SD as measured by mWHO, novel patterns of clinical activity, which are related to the immunological mechanism of action of ipilimumab, were reported in all 3 studies. These patterns of activity were characterized by overall reductions from baseline in total tumor burden (index plus measurable new lesions, when present) after the appearance of new lesions and/or after an initial tumor burden increase. Of 227 treated subjects who received 10 mg/kg ipilimumab in studies CA184022 and CA184008, 9.7% of subjects demonstrated disease control after an initial increase in tumor burden and/or appearance of new lesions

(Wolchok et al., 2010; O'Day et al., Ann Oncol 2010; CA184022 Clinical Study Report 2008; CA184008 Clinical Study Report, 2008; CA184007 Clinical Study Report 2008).

Survival data from these 3 primary studies (CA184022, CA184008, and CA184007) are supported by OS data from CA184004 and MDX-010-28. Both studies enrolled previously untreated and pretreated subjects with advanced melanoma. In CA184004, 42 subjects were randomized to 10 mg/kg ipilimumab. The median follow-up for survival in this study was 8.6 months. The median OS was 11.8 months (95% CI: 6.1, --); the 1-year survival rate was 44.2% (95% CI: 24.1%, 64.1%) (CA184004 Clinical Study Report, 2008). Data are available for 23 response-evaluable subjects treated at 10 mg/kg ipilimumab in MDX010-15 who enrolled in the follow-up study MDX010-28. The median follow-up for survival in this study was 13.4 months. The median OS was 13.2 months (95% CI: 9.4, 19.4). The overall survival for 2 subjects with ongoing responses was 26.0+ months and 25.0+ months (MDX010-19 Clinical Study Report, 2007).

In this protocol the proposed induction dosing of 3 mg/kg every 3 weeks for 4 doses followed by reinduction for eligible patients is based on the Phase 3 study MDX010-20 published in NEJM 2010 (Hodi et al.) and supported by the safety and activity of 3 mg/kg ipilimumab from two Phase 2 studies (CA184022 and CA184004). MDX010-20 demonstrated a statistically significant and clinically meaningful survival benefit with a hazard reduction for death of 34% (hazard ratio of 0.66) in subjects with pre-treated advanced melanoma who received ipilimumab monotherapy with a 1-year survival rate of 45% and a 2-year survival rate of 23% which was statistically highly significant compared to the control arm (Hodi et al., 2010).

Further, clinical activity was also observed upon re-induction of ipilimumab therapy in MDX010-20 (Hodi et al., 2010). In parallel with MDX010-20, the randomized, Phase 2, dose-ranging study CA184022 investigated doses of 0.3, 3, and 10 mg/kg doses administered every 3 weeks for 4 doses (induction) followed by one dose every 12 weeks (maintenance). There was increasing clinical activity with increasing doses of ipilimumab based on the PK, PD,19 and BORR (Wolchok et al., Lancet Oncology 2010). The results were consistent with those from MDX010-20 and across the Phase 2 program.

The regimen of 3 mg/kg ipilimumab every 3 weeks for 4 doses used in the Phase 3 study is the best characterized to date, with ipilimumab demonstrating an OS benefit. Therefore, the recommended dose and schedule of ipilimumab for the treatment of patients with advanced melanoma who have received prior therapy reflects that used in the pivotal Phase 3 study: 3 mg/kg ipilimumab administered IV over a 90-minute period every 3 weeks for a total of four doses as tolerated (induction), with additional treatment (re-induction of the same dose and schedule as tolerated) considered for patients who develop progressive disease after prior complete response, partial response, or stable disease lasting longer than 3 months from the first tumor assessment.

Further details on clinical results can be found in the current version of the Ipilimumab Investigator Brochure.

#### **1.3.6.a Relationship Between Response and Immune Related Events in Patients with Metastatic Melanoma**

Drug-related AEs of any grade considered to be immune-mediated in nature (irAEs) were reported for 59.6% (1729/2901) of subjects in clinical studies of ipilimumab. These irAEs are a consequence of inhibiting CTLA-4 function and most were reported as Grade 1 or 2. An association between best overall response (BORR) and higher grade (Grade 3-4) irAEs was suggested in early studies of ipilimumab 3 mg/kg but this association was not observed in 4 Phase 2 studies of ipilimumab administered at 10 mg/kg (CA184022, CA184008, CA184007 and CA184004). There were proportionally more subjects with irAEs of any grade who experienced response or stable disease than subjects without irAEs who experienced response or stable disease, but due to the small sample sizes, these observations were statistically inconclusive (Wolchok et al., 2010; O'Day et al., Ann Oncol 2010; CA184022 Clinical Study Report 2008; CA184008 Clinical Study Report, 2008; CA184007 Clinical Study Report 2008). Generally, disease control and long term survival are observed among patients regardless of whether they do or do not develop Grade  $\geq 2$  irAEs.

#### **1.3.7 Rationale for using immune-related Tumor Assessment Criteria (irRC)**

Ipilimumab is an immuno-stimulating antibody with evidence of anti-cancer activity (durable objective response and stable disease) in subjects with advanced melanoma, including subjects with established brain disease. Observations of clinical activity defined by tumor response endpoints defined by conventional criteria (eg, mWHO) may be inadequate to realize the kinetics and magnitude of clinical benefit achieved with ipilimumab.

Histopathological evidence has demonstrated ipilimumab can produce an influx or expansion of tumor infiltrating lymphocytes (Townsend et al., 1993). Therefore, early increases in lesion size detected radiologically or upon gross examination could be misinterpreted as progressive tumor growth and precede objective tumor shrinkage. In addition the appearance of new lesions may have categorized a subject to have progressive disease using conventional tumor assessment criteria despite the concurrent observation of objective tumor responses in preexisting lesions and a net reduction in global tumor burden that includes the new lesions.

Hence the appearance of new lesions in and of themselves may not necessarily constitute progressive disease. The immune-related response criteria (irRC) were developed as a tool to gauge tumor response using the changes in global tumor burden (Wolchok et al., 2009). In addition, the irRC may be useful to inform a physician's decision to continue dosing in subjects who may receive benefit from additional ipilimumab therapy. The ir-response assessment is

based solely on objective measurements (SPD) of index and new lesions. Non-index lesions are not considered. The irRC identified 9.7% of subjects (22/227 treated subjects) from CA184022 and CA184008 at 10 mg/kg who demonstrated disease control in the form of stable or reduced measurable tumor burden, including new lesions, at or after disease progression by mWHO.

#### **1.4 Overall Risk/Benefit Assessment**

As indicated above, ipilimumab has increasing clinical activity with increasing doses, however, there is also an increasing incidence of serious adverse events by increasing dosage.

The regimen of 3 mg/kg ipilimumab every 3 weeks for 4 doses used in the Phase 3 study (MDX010-020) is the best characterized to date, with ipilimumab demonstrating an OS benefit (Hodi et al., NEJM, 2010). Therefore, the recommended dose and schedule of ipilimumab for the treatment of patients with advanced melanoma who have received prior therapy reflects the regimen used in the pivotal Phase 3 study: 3 mg/kg ipilimumab administered IV over a 90-minute period every 3 weeks for a total of four doses as tolerated (induction), with additional treatment (re-induction of the same dose and schedule as tolerated) considered for patients who develop progressive disease after prior complete response, partial response, or stable disease lasting longer than 3 months from the first tumor assessment and no severe toxicity experienced.

The proposed induction dosing in this study of 3 mg/kg every 3 weeks for 4 doses followed by re-induction for eligible patients is based on the Phase 3 study MDX010-20 and supported by the safety and activity of 3 mg/kg ipilimumab from two Phase 2 studies (CA184022 and CA184004). MDX010-20 demonstrated a statistically significant and clinically meaningful survival benefit with a hazard reduction for death of 34% (hazard ratio of 0.66) in subjects with pre-treated advanced melanoma who received ipilimumab monotherapy (Hodi et al., NEJM, 2010) in comparison to gp100 monotherapy arm. Further, clinical activity was also observed upon re-induction of ipilimumab therapy in MDX010-20 (Hodi et al. JCO 2010) In parallel with MDX010-20, the randomized, Phase 2, dose-ranging study CA184022 investigated doses of 0.3, 3, and 10 mg/kg doses administered every 3 weeks for 4 doses (induction) followed by one dose every 12 weeks (maintenance) (Wolchok et al., 2010). There was increasing clinical activity with increasing doses of ipilimumab based on the PK, PD, and BORR (Wolchok et al., 2010). The results were consistent with those from MDX010-20 and across the BMS Phase 2 program.

Characteristic organ-specific inflammatory irAEs were reported with ipilimumab therapy, typically during induction therapy. IrAEs were mostly reversible within days to weeks following cessation of therapy or treatment with symptomatic therapy, corticosteroids or other anti-inflammatory agents, depending upon severity. Accumulated clinical experience resulted in

detailed toxicity management guidelines (also termed algorithms), by use of which irAEs can be effectively managed, especially when irAEs are recognized early and subjects are treated in a timely fashion. This can minimize the occurrence of irAE complications, such as GI perforation/colectomy or hepatic failure.

Since currently no cure for patients suffering from advanced melanoma is available and no drug ever has shown any survival benefit in prospective controlled randomized clinical phase III studies, ipilimumab at its 3mg/kg given four-times every 3 weeks is currently the best choice for melanoma patients who have failed systemic treatment in order to improve one- and two-year survival. Considering this background an irAE event rate of less than 25% grade 3-4 is highly acceptable.

In the context of the historical data which demonstrate a 2-year survival rate of approximately 8% to 18% in subjects with previously untreated advanced melanoma (Korn et al., 2008; Chapman et al., 1999; Middleton et al., 2000; Bedekian et al., 2006) 2-year survival rates for ipilimumab treated patients in clinical studies ranges from 29.81% to 41.78%.

The overall risk-benefit ratio for patients entering this protocol is therefore at least comparable to and possibly better than alternative options.

## **1.5 Study Rationale**

Melanoma is the most common tumor of the skin that develops from a neoplastic transformation of melanocytes. The incidence of cutaneous melanoma is increasing at a faster rate than for any other solid tumor and is estimated as 68,000 new cases annually in the USA. Globally, the incidence of melanoma varies by region, and according to World Health Organization (WHO) over 130,000 new cases of melanoma are recognized annually around the world. Melanoma is a tumor with significant impact on society and when found to be metastatic, there is no effective treatments for most patients. Although most patients have localized disease at the time of diagnosis and are cured by surgical excision of the primary tumor, metastases can develop and most of these patients die of melanoma-associated causes. In the USA, over 8,000 deaths in 2008 were associated with melanoma.

Most melanomas develop in the skin (cutaneous melanoma). The AJCC classification is helpful in segregating risk for recurrence and survival in primary melanoma, especially when combined with the Breslow thickness criteria. The American Joint Committee on Cancer (AJCC) first published a staging schema in 1978 that incorporated primary tumor thickness, ulceration, level of invasion, regional and distant metastases subtypes and serum LDH levels that correlated with prognosis for relapse and survival (Balch et al J Clin Oncol 2009). For

metastatic melanoma, however, there is no current classification scheme that allows to predict a response to treatment in more than 25% in a given cohort. Melanomas from any anatomic site may metastasize. The overall median survival from diagnosis of stage IV melanoma has been estimated to be 8 months. One year survival for these patients has been reported as approximately 25%, with approximately 15% of patients surviving 5 years (SEER 2009). In metastatic melanoma, chemotherapy is used mostly with palliative intent. Currently registered agents for the treatment of melanoma include the alkylating agent dacarbazine (DTIC) and high dose IL-2 (US only). The administration of dacarbazine (DTIC) is a standard treatment with response rates in the range of 5-15% and progression free survival of approximately 8 weeks (Chapman et al, 1999). Cytotoxic therapies have not been reported to prolong overall survival.

This trial is designed in light of the high unmet medical need in the treatment of metastatic melanoma and the promising clinical results derived from trials with ipilimumab. Various phase II clinical studies using ipilimumab in unresectable stage III-IV have been conducted. Results of the first pivotal phase III study MDX010-20 were presented at ASCO 2010 (O'Day et al., JCO 2010) and published in parallel by Hodi et al. (NEJM, 2010). In the second ongoing phase III trial CA184-024, a different dose and treatment scheme is currently tested in the first-line setting. Results are expected at the end of 2010.

However, due to strictly defined inclusion and exclusion criteria in phase III trials, results of registrational trials might not answer all questions regarding safety and efficacy of ipilimumab in all advanced melanoma patient cohorts seen in daily routine. E.g. on one hand, in MDX010-20 trial, only patients positive for HLA-A2 could be enrolled (since patients were randomized in a double-blind fashion in a 1:3:1 ratio to receive HLA2-restricted melanoma gp 100 peptide vaccine monotherapy, MDX-010 in combination with melanoma gp100 peptide vaccine, or MDX-010 monotherapy.) In the second currently ongoing phase III study 184-024 patients were not restricted to HLAA2+ haplotype. However, a different patient group was enrolled (first line situation) and another dosing and treatment scheme was tested (combination with DTIC; ipilimumab 10mg/kg and maintenance period following induction phase for patients who benefitted from ipilimumab). Patients with primary mucosal melanoma were excluded in CA184-024 study; patients with primary ocular melanoma were excluded in both Mdx010-20 as well as in CA184-024.

A large clinical phase II trial is proposed to treat broad range of metastatic melanoma patients who have failed at least one systemic treatment regimen in advanced, non-resectable melanoma. This study aims to gain more information about efficacy and safety of ipilimumab in a broad range of clinically relevant pretreated patient cohorts seen in daily routine, neither addressed in MDX-010-20 study nor in CA184-024. Enrollment will not be restricted to any specific HLA subtype and patients with uveal or ocular melanoma as well as cutaneous

melanoma patients with or without asymptomatic brain metastases can be treated with ipilimumab as well. Potential predictive markers (ALC, B-raf mutational status) will be prospectively evaluated. Wide access to ipilimumab in skin cancer-specialized clinical centers will be achieved in addition to a standardized evaluation of its clinical results and of the proposed management guidelines handling the side effects. Patients will be treated according the MDX010-20 protocol with ipilimumab monotherapy 3mg/kg four times during the induction phase only. Patients who benefit from therapy (stable disease of  $\geq 3$  months beginning at Week 12 or patients with initial partial or complete response at Week 12 assessment) and did not show any immune-related adverse event (irAE)  $\geq$  grade 3 will be eligible for treatment re-induction in the case of melanoma relapse.

## 2 STUDY OBJECTIVES

### 2.1 Primary Objective

To further characterize efficacy of second line ipilimumab monotherapy 3mg/kg given according to the MDX010-20 protocol in a broad range of pretreated metastatic melanoma patients seen in daily clinical practice:

- Overall survival rate at 12 months defined as the rate of patients alive 12 months after the date from the first study treatment for complete study population

### 2.2 Secondary Objectives

To explore safety and additional efficacy parameters of the ipilimumab treatment in certain subgroups: (cutaneous versus uveal versus mucosal melanoma; LDH < 2 ULN versus LDH ≥ 2 ULN; status brain metastases versus no brain metastases in medical history; b-raf mutation positive versus b-raf mutation negative)

Secondary objectives are

- Safety / toxicity according to the CTC Criteria (Version 4.0)
- Efficacy according to immune-related response criteria (ir-RC) at any time during treatment
- Efficacy according RECIST criteria
- Progression free survival rate at 6 months
- Overall survival
- To explore clinical efficacy of ipilimumab in relation to b-raf mutation status, brain metastases and LDH

### 2.3 Exploratory Objectives

- To examine the value of peripheral blood absolute lymphocyte count (ALC) as a predictive biomarker in various patient cohorts with unresectable stage III-IV melanoma treated with ipilimumab monotherapy
- 
- To evaluate possible surrogate markers in peripheral blood and tumour biopsy (translational research program)

### **3 STUDY DESIGN**

#### **3.1 Overall Study Design**

This is an open-label, multi-center, single-arm clinical phase II study to further characterize the efficacy and safety of ipilimumab (3 mg/kg iv every 3 weeks over 10 weeks) in patients with pretreated, metastatic and/or inoperable melanoma. .

The study will have one final analysis. The final analysis will occur 12 months after the last patient has been entered the clinical study. Prior to closure of the study, it will be ensured that survival data has been collected for each subject for 1 year following the subject's first treatment dose. A Safety Data Monitoring Committee (SDMC) will be responsible for reviewing all Grade 3-4 irAE on a regular basis. Based on its review the DMSB will provide the sponsor with recommendation regarding trial modification, continuation or termination.

**Figure 2 Study design**[figure not shown]

Tx = treatment with study medication

### 3.2 Enrollment of Patients

The selection of patients occurs through the investigator according to the inclusion and exclusion criteria after informing the patient written and orally about the study and after the patient has signed the informed consent. Patients considered eligible by the Investigator once all screening procedures are complete will be enrolled by online registration.

**Online registration is possible 24 hours a day.** After the registration form has been saved, the registration is notified immediately by an automatically generated fax to the investigator. The site should begin the patient on study treatment within 14 days of registration.

### 3.3 Number of Patients

The enrollment of up to 200 patients with unresectable stage III-IV melanoma is planned.

### 3.4 Timelines

|                              |               |
|------------------------------|---------------|
| Period of recruiting         | 8-9 months    |
| Enrolment start date (FPI):  | QII 2011      |
| Enrolment finish date (LPI): | December 2011 |
| End of study:                | QIV 2012      |

### 3.5 Definition of the End of Study

End of study will be at recruitment finished plus 1 year post start of treatment of last patient thus ensuring that 1 year survival rate can be estimated. In case that the last patient will not start treatment, the trial will end 12 months after the last patient entered the trial. Therefore expected maximum study duration is 8-9 months accrual + 12 months for follow-up.

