### **Treatment:**

Treatment with the anti-CTLA-4 mAb Ipilimumab monotherapy of each patient in the scope of this trial is defined as induction plus re-induction of eligible patients until 12 months after first receipt of study medication

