### 3.6 Plan for Treatment after the End of Study

Further patient treatment will be at the discretion of the Investigator. All patients in re-induction phase when their study period is ending, will be offered free ipilimumab to complete the re-induction treatment. Off-study patients eligible for a re-induction may be treated with ipilimumab if deemed appropriate by the treating physician, either using commercial drug if licensed in Germany or via the Early Access Program if the Marketing Authorization is not granted yet.

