During the Re-Induction treatment, subjects enrolled who are eligible for additional treatment cycles will repeat the treatment phase as outlined in INDUCTION TREATMENT. They will receive ipilimumab at the 3 mg/kg dose level every 3 weeks for the first 10 weeks (Weeks 1, 4, 7 and 10) of Re-induction.

Ipilimumab therapy should be offered to all subjects who have not experienced unacceptable toxicity (refractory Grade > 3 irAEs) and are considered by the investigator to be obtaining clinical benefit, either because of apparent tumor stability or continued shrinkage and/or late response. No patient will be re-treated if they experience a Grade 3 or higher nondermatologic autoimmune breakthrough event (ABE) considered related to study therapy or a Grade 3 or higher gastrointestinal or certain other immune-related adverse events (irAE) which require permanent discontinuation of ipilimumab (refer to section 5.5.3). If a patient has experienced a study medication-related dermatologic or non-dermatologic ABE < Grade 3, then the event must have improved to Grade 1 or less before re-treatment can be considered. No patient with disease progression following the first cycle of study medication will be permitted to be re-treated with study medication.

Patients can be eligible for more than one re-induction. The number of re-inductions is not limited. All re-inductions initiated while patient is on-study (**each patient study period**, first dosing + 12 months) will be performed in the frame of the study. Any re-induction starting after each patient study period (first dosing + 12 months) would be done outside of the study.

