#### 8.3.1. Serious Adverse Events

Following the subject's written consent to participate in the study, all SAEs must be collected, including those thought to be associated with protocol-specified procedures. All SAEs must be collected that occur within 70 days of discontinuation of dosing of the investigational product. If applicable, SAEs must be collected that relate to any later protocol-specified procedure (eg, a follow-up skin biopsy). The investigator should notify the study sponsor of any SAE occurring after this time period that is believed to be certainly, probably, or possibly related to the investigational product or protocol-specified procedure.

All SAEs whether related or unrelated to the ipilimumab, must be immediately reported to the sponsor by using the online documentation system (by the investigator or designee) within 24 hours of becoming aware of the event. If only limited information is initially available, follow-up reports are required.

The sponsor will notify all **serious adverse events to BMS (Pharmacovigilance Germany; [contact]).**

For reporting, each serious adverse event must be documented on the electronically available "**Serious adverse events report**" form. The completed form is automatically faxed (fax no. is filed automatically in the system) to the sponsor, to BMS and to Alcedis GmbH. In the event that electronic reporting is not possible, paper SAE forms in the investigator's file handed out at the beginning of the study are at the doctor's disposal for notification by conventional fax. In

some instances where a facsimile machine is not available, overnight express mail may be used.

The initial report to the sponsor, to BMS and to Alcedis GmbH must be followed **within 5 days** by a detailed written communication (in English) containing a precise description of the adverse events, all countermeasures taken and their outcome. In the event of death, if an autopsy has been performed, a copy of the autopsy report should be attached.

The sponsor will notify all **serious adverse events to BMS ([contact], [contact] Uhr); 24-Stunden, emergency line: [name]; [contact])**

Serious adverse events, whether related or unrelated to investigational product, must be reported on the SAE form expeditiously to comply with regulatory requirements. An SAE report should be completed for any event where doubt exists regarding its status of seriousness.

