Additional analyses treating survival and PFS as time to event endpoints will be performed i.e.: Kaplan-Meier plots will be produced. These will use the ITT population. Survival will be measured, regardless of any re-induction, from the date of the first on-study ipilimumab dose until date of death. Survival time for subjects, whose date of death is unknown, will be censored at the last date of contact. PFS will be measured, regardless of any re-induction, from the date of the first dose of ipilimumab until the first on-study documented date of progression, as per irRC, or date of death, whichever comes first. PFS time of subjects not known to progress or die, will be censored at the date of the last tumor assessment. Median survival, median PFS, survival rate at 1 year and PFS rate at 6 months, all as derived from the Kaplan-Meier curves, will be presented, together with 95%CI.

Safety will be reported for 70 days (5 half-lives) post last treatment. This period will be considered the on-study safety period. The analysis of safety will be based on the frequency of AEs and their severity for all treated subjects (i.e.: the Safety population). Worst toxicity grades per subject will be tabulated for all AEs. Additionally, drug-related grade 3 or more AEs, immune-related, and serious AEs will be tabulated separately, and listings by subject will be produced for all deaths, all SAEs and all AEs leading to discontinuation of study drug.

All adverse events and serious adverse events recorded during the study will be summarized using descriptive statistics. The incidence of treatment-emergent adverse events (new or worsening from baseline) will be summarized by body system, preferred term, verbatim of adverse event, intensity (based on CTC grades), and relation to the investigational products. Furthermore all adverse events and serious adverse events will be listed.

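### The study closes 12 months after the last patient's first dose, too early for the 70-day safety window after late re-inductions in late-enrolled patients

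*Protocol*

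**What the plan says.** **What counts as study treatment.** Section 5.2 covers "All re-inductions initiated while patient is on-study", defines that period as first dose plus 12 months, and does not limit their number. It draws the line at the start date: "Any re-induction starting after each patient study period (first dosing + 12 months) would be done outside of the study".

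**How long safety is followed.** Section 9.5: "Safety will be reported for 70 days (5 half-lives) post last treatment". Section 8.3.1: "All SAEs must be collected that occur within 70 days of discontinuation of dosing of the investigational product". Section 6.1.1.4 puts the end-of-treatment visit 10 weeks after the last dose. None of the three carries a 12-month limit.

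**When observation ends.** Section 3.5: "End of study will be at recruitment finished plus 1 year post start of treatment of last patient". Section 3.1: "The final analysis will occur 12 months after the last patient has been entered the clinical study". For the individual patient, the synopsis sets follow-up at 1 year from first dose, and Section 6.1.1.3 caps re-staging visits at the same point.

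**Status of doses after month 12.** The synopsis defines treatment within the trial as "induction plus re-induction of eligible patients until 12 months after first receipt of study medication". Section 3.6, under its heading on treatment after the end of study, says: "All patients in re-induction phase when their study period is ending, will be offered free ipilimumab to complete the re-induction treatment".

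**The concern.** The end of study is set by one consideration, the 1-year survival rate. It makes no allowance for the safety window that the plan attaches to the last dose of an in-study re-induction. A course can start on the last day of a patient's 12 months and still be study treatment under Section 5.2, with four doses and 70 days of observation to come.

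Two things are at stake. First, patients whose window is cut remain in the all-treated denominator, so their unobserved events can only lower the reported rates, and the loss falls on repeat dosing. Second, sites can read Sections 3.6 and 5.2 differently on whether a completing dose is a study dose, and so collect different data after month 12.

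**Working it through.** **The plan's own duration.** 8-9 months of accrual + 12 months = 20-21 months. Last patient in December 2011 + 12 months = December 2012, the stated QIV 2012. The figure reproduces and leaves no slack.

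**Span of one re-induction.** Doses fall on days 1, 22, 43 and 64, so dosing takes 3 x 21 = 63 days. Adding the 70-day window gives 63 + 70 = 133 days.

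- Latest start fully covered by day 365: 365 - 133 = day 232 (week 33).
- Less 28 days for the required confirmation of progression: progression first seen by day 204 (week 29).
- Start on day 365: last dose day 428, window ends day 498.

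**Scheduled scans (Section 5.1), with 28 days' confirmation.** The ranges reflect two ways of turning weeks into days.

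| Progression seen at | Start (day) | Last dose | Window ends | Past day 365 |
|---|---|---|---|---|
| Week 24 | 189-196 | 252-259 | 322-329 | none |
| Week 36 | 273-280 | 336-343 | 406-413 | 41-48 days |
| Week 48 | 357-364 | 420-427 | 490-497 | 125-132 days |

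After week-36 progression, 22-29 of the 70 post-dose days fall before day 365. After week-48 progression, one of the four doses does.

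**Reading A: collection stops at each patient's month 12.** All week-36 and week-48 cases are cut. The documents give no progression times, so two assumptions are used.

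- Constant hazard after week 12 with median m months. The chance of progression per 12-week interval is h = 1 - 0.5^(2.77/m), and the weights for weeks 24, 36 and 48 are h, (1-h)h and (1-h)^2 h, rescaled to 1. For m = 3 they are 0.55, 0.29, 0.15; for m = 12 they are 0.39, 0.33, 0.28. Share cut: 1 - 0.55 = 45% to 1 - 0.39 = 61%.
- Starts spread evenly from day e to day 365, where e = 78 + 28 = 106 (progression at about week 12) to 78 + 91 + 28 = 197 (after 3 months of stable disease). Share cut = 133/(365 - e): 133/259 = 51% to 133/168 = 79%.

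Together: 45-79%.

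**Reading B: collection runs to study closure.** A patient enrolled u days before the last patient has u extra days. With uniform accrual over 8-9 months (243.5-274 days), the share cut is the overrun divided by the accrual time.

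- Week 36: 41/274 = 15% to 48/243.5 = 20%.
- Week 48: 125/274 = 46% to 132/243.5 = 54%.
- Overall, with 8.5 months (258.7 days) of accrual and overruns of 42 and 126 days: m = 3 gives (0.29 x 42 + 0.15 x 126)/258.7 = 12%; m = 12 gives (0.33 x 42 + 0.28 x 126)/258.7 = 19%.
- Even starts: (133^2/2)/[258.7 x (365 - e)] = 13% for e = 106 and 20% for e = 197.

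Together: about 12-20%.

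**Patients.** The protocol gives no re-induction rate. If 3-10% of 200 are re-induced (6-20 patients), reading B cuts about 1-4 (0.12 x 6 to 0.20 x 20) and reading A about 3-16 (0.45 x 6 to 0.79 x 20).

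**The case against.** The strongest reply is that no section stops safety collection at a patient's month 12. The individual 12-month limits concern survival follow-up and re-staging visits. Section 8.3.1 ties SAE collection to the end of dosing and also asks for later SAEs thought to be related. Early enrollees have up to 8-9 further months before closure. Even for a start on day 365, (243 - 133)/243 = 45% to (274 - 133)/274 = 51% of patients would have a full window. This stands, and it is why reading B is the favourable case. It narrows the gap without closing it.

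A reader might also infer that no visit exists at 70 days, or that patients are dosed under a closed protocol. The text does not support either. Section 6.1.1.4 schedules the 10-week visit. Section 3.6 speaks of the patient's own study period, treats off-study patients in a separate sentence, and can be read as securing drug for a course already in the study. Its heading and the synopsis definition point the other way, so the status of those doses is unclear rather than settled.

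Nor does every re-induction after stable disease overrun. That holds for progression found at scheduled scans with 3 months taken as 13 weeks, since week 24 is only 84 days after week 12. Section 5.2 also accepts progression found by physical examination or other imaging, and detection between about weeks 25 and 29 would fit.

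Finally, a data cut-off is often left to the SAP. Here, however, the protocol itself fixes both the closure date and the timing of the single analysis.

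**Conclusion.** The point holds for late re-inductions in late-enrolled patients. On every reading, some courses that Section 5.2 counts as in-study cannot have the 70-day window that Sections 8.3.1 and 9.5 require before the study closes. The share is about 12-20% of re-inductions if collection runs to closure and about 45-79% if it stops at each patient's month 12. Both ranges rest on assumed progression times, one uninterrupted course and, for the first, uniform accrual.

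A reader might infer that most re-induced patients lose their window, or that safety is materially understated. The first needs the month-12 stop, which no section states, and does not hold across the whole range even then. On the second, only the direction is certain. Under the assumed 3-10% re-induction rate, 6-20 is the number re-induced, not the number cut. With 1-4 patients cut, no all-treated rate could shift by more than 4/200 = 2 percentage points; under the month-12 stop the ceiling is 16/200 = 8 points. Either ceiling would require every cut patient's only counted event to fall in the lost days. The actual shift cannot be computed and is probably small.

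Separately, Section 3.6 and the synopsis treatment definition conflict with Section 5.2 on doses that complete a course after month 12. The 1-year survival endpoint is untouched.

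**What to change.** Reconcile the synopsis (treatment and follow-up) with Sections 3.5, 3.6, 5.2, 6.1.1.4, 8.3.1 and 9.5, so that it is unambiguous whether doses completing a re-induction after month 12 are study treatment and which collection rules and visits apply to them. Which status is right is for the sponsor to decide.

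Then define the safety data cut, and the end of study for safety, as the later of (a) the last patient's first dose plus 12 months and (b) 70 days after the last dose of any re-induction that counts as in-study. Keep the 12-month cut for the primary survival analysis, and let Section 3.1 allow the safety tables to follow it.

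The cost is protocol wording and longer safety follow-up for a few patients. For one uninterrupted course the safety lock moves by at most 133 days, about 4.4 months. The survival analysis is not delayed.
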